### Statistical analyses

The primary analyses will be performed according to the ‘intention to treat’-principle, indicating that participants will be included in the analysis according to the by randomization allocated group. Secondary analyses will be limited to the compliant participants, independent of which intervention they were randomized (per protocol analysis). Distribution analysis of all variables will be tested by the Shapiro–Wilk test.

Primary outcome will be analyzed by linear regression analyses with change in CMS between baseline and 12 month follow up as dependent variable. The assumptions of constant variance and linear relationships will be assessed using scatter plots. Should any of these assumptions seriously fail then variable transformations will be used. Analyses will be adjusted for baseline variables that change the effect estimate with more than 10%. Similar analyses will be performed for the secondary continuous outcome parameters. Differences between groups on complications and additional treatment will be analyzed by means of Mann–Whitney tests. Furthermore, differences in recovery trajectories between groups will explored by means of mixed ANOVA. Statistical analyses will be performed using SPSS software (IBM, USA). An alpha level of 0.05 will be accepted as significant.

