### Sample size calculation

For the sample size calculation, we used the minimal clinically important difference (MCID) for the Constant Murley Score as determined by the study of Kukkonen et al [24].

The reported MCID over a period of 12 months was 10.4 points, with a mean Constant Murray Score of 53.1 (standard deviation of 17.2) at baseline [24].

We aim to find a superiority of one of the two treatment options to treat patients with calcifying tendinitis of the shoulder. Our hypothesis is that superiority of NACD or ESWT above the other treatment in functional recovery over a period of 12 months will be found. Superiority will be expressed by an additional effect size of minimally 0.5. Using a standard deviation of 17.2 of the CMS, we aim to detect a minimally difference of 8.6 points between both groups. Using a power of 80% and an alpha of 0.05 the required sample size is 63 patients per group, resulting in a total of 126 patients. With this number of patients, we will also able to detect a MCID between both groups of 10.4 points (required number of patients is 43 per group). The final sample size required is 140 patients, to accommodate 10% potential dropout rate over 1 year.

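### Run as named, the primary change-score regression and the mixed ANOVA cannot use the 8-week and 6-month CMS of patients who lack a 12-month score; a repeated-measures mixed model would

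*Protocol article*

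**What the plan says.** Under Statistical analyses, the primary outcome is to be analysed by "linear regression analyses with change in CMS between baseline and 12 month follow up as dependent variable". The intention-to-treat principle is explained only as meaning that "participants will be included in the analysis according to the by randomization allocated group". For the course over time, "differences in recovery trajectories between groups will explored by means of mixed ANOVA". The named software is SPSS.

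Table 2 (data collection schedule) has the CMS at baseline, 8 weeks, 6 months and 12 months.

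Under Sample size calculation: "Using a standard deviation of 17.2 of the CMS, we aim to detect a minimally difference of 8.6 points between both groups", and "Using a power of 80% and an alpha of 0.05 the required sample size is 63 patients per group, resulting in a total of 126". Then: "The final sample size required is 140 patients, to accommodate 10% potential dropout rate over 1 year".

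**The concern.** Both named methods need complete rows. The primary regression needs the baseline and the 12-month CMS. The mixed ANOVA, in its ordinary between-within form, needs all four visits. A patient seen at 8 weeks and 6 months and then lost contributes to neither, although those scores are in the database. Analysing patients by allocated group does not bring that patient back.

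At stake is the primary between-group difference. The trial is open-label, and the section on rehabilitation after the intervention allows repeat treatment, cross-over and surgery during follow-up. Loss that is related to response and unequal between the arms is therefore possible. If poor responders leave one arm more than the other, the completers' mean flatters that arm. The 6-month CMS carries information about who those patients were, and the named models ignore it.

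**Working it through.** **Inputs from the protocol article.** SD 17.2, target difference 8.6, power 80%, alpha 0.05 (taken as two-sided), 10% dropout, 140 randomised, four CMS visits. The article gives no correlations between visits, dropout mechanism or missed-visit rate; these are assumptions below.

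**1. The plan's own figures.** n per group = 2(1.960 + 0.842)² × (SD/difference)².
- 8.6 points: 2 × 7.849 / 0.25 = 62.8, so 63.
- 10.4 points: 2 × 7.849 × (17.2/10.4)² = 42.9, so 43.
- Inflation: 126 / 0.9 = 140.

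All three reproduce.

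**2. Power.** With 63 completers per arm, SE = 17.2 × √(2/63) = 3.06 and power = Φ(8.6/3.06 − 1.96) = 80.1%. With full information on 70 per arm, SE = 17.2 × √(2/70) = 2.91 and power = 84.1%. Partial follow-up recovers only part of that gap.

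**3. Patients affected.** Primary regression: 10% of 140 = 14, leaving 126. Mixed ANOVA: if a share m also misses each of the two interim visits independently (assumed), the loss is 1 − 0.9(1 − m)². This is 18.8% for m = 5% and 27.1% for m = 10%.

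**4. Bias in closed form.** Assume normal scores with common SD 17.2, correlation 0.5 between baseline and any follow-up, and 0.6 between follow-ups. If selection acts on a 6-month quantity X in one arm only, bias = (slope of the 12-month change on X) × (shift in mean X among those who stay). The ceiling is reached if exactly the worst 10% on X leave: shift = 0.195 SD = 0.195 × 17.2 = 3.35 points (the SD of the 6-month improvement is also 17.2 at correlation 0.5).
- X = 6-month improvement: slope = (0.6 − 0.5 − 0.5 + 1) / (2 − 2 × 0.5) = 0.6; ceiling 0.6 × 3.35 = 2.0 points.
- X = 6-month CMS level: slope = 0.6 − 0.5 = 0.1; ceiling 0.1 × 3.35 = 0.3 points. With all correlations equal it is zero.
- Adjusting completers for baseline CMS (coefficient 0.5) gives slope 0.6 − 0.5 × 0.5 = 0.35 for level-driven loss, and the same for improvement-driven loss (0.6 − 0.5 − 0.25 + 0.5 = 0.35). Baseline adjustment alone therefore does not remove the bias.

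**5. Simulated trials** (70 per arm, 10% without a 12-month CMS; correlations varied).

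| Dropout | Bias, complete-case change score |
|---|---|
| Random | negligible |
| Same mechanism in both arms | about 0.1 or less |
| One arm, driven by 6-month level | about 0.2 to 0.7 |
| One arm, driven by 6-month improvement | about 0.7 to 2.0 |
| Opposite directions in the two arms (extreme) | 1.1 to 2.5 (estimates 9.7 to 11.1, truth 8.6) |

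An estimator using all visits stayed within about 0.1 of the truth throughout.

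**6. Precision.** Under random dropout (assumed correlations 0.3 for 0–12 months and 0.6 to 0.8 for 6–12 months), the SE fell from about 3.5–3.65 to 3.3–3.6, a small gain.

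**The case against.** The strongest reply is that the article never says that only completers will be analysed. Rules for missing data usually sit in the analysis plan or the full protocol, neither of which is shown, and multiple imputation using the interim CMS could precede the same regression. That stands: silence on imputation is no fault here, and inflating 126 to 140 proves nothing, since trials planning imputation also inflate. What remains is that the methods actually named, run as named, leave collected outcome data unused, and a better method is available at almost no cost.

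Second, the size depends on the scenario. This also stands. The larger figures need dropout driven by poor improvement in one arm only, and even 1.5 points is about half the SE of 3.06. Nothing in the article shows that dropouts will be poor responders. Further treatment is started by the treating surgeon and recorded in the study, and the Discussion describes follow-up by phone or video for 12 patients when visits were impossible. A reader might infer that the primary result will be biased; the documents support only that it could be.

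Third, the mixed ANOVA is exploratory, so no primary conclusion depends on it, and its 19–27% loss rests on an assumed missed-visit rate. If a linear mixed model was meant, that part is a matter of wording. A reader might also object to sphericity because the visits are unequally spaced, but unequal spacing does not itself violate sphericity and SPSS offers corrections.

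**Conclusion.** The point holds in a limited form. As named, the primary regression cannot include a patient without a 12-month CMS, and a classical mixed ANOVA drops any patient missing one of four visits, although interim CMS values are collected and about 14 of 140 patients are expected to be lost.

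Under the assumed correlations and 10% dropout, the bias is roughly 0.2 to 2 points (2% to 23% of 8.6) if outcome-related dropout differs by arm. It is negligible if dropout is random or shares one mechanism. Only the extreme opposite-direction case went higher, and equal correlations with level-driven dropout bring it to about zero.

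A reader might infer that the trial is underpowered or that the intention-to-treat claim is false. Neither follows: 126 completers give 80.1%, dropout was allowed for, and the article fixes the grouping of patients without stating a completers-only rule. The change is worth making because it is cheap and protects the primary estimate, not because an error in the result has been shown.

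**What to change.** Make the primary analysis a linear mixed model for repeated measures (SPSS MIXED, REML):
- outcomes: CMS at 8 weeks, 6 months and 12 months;
- fixed effects: group, visit, group-by-visit, baseline CMS and baseline-by-visit;
- unstructured covariance within patient;
- primary test: the group contrast at 12 months.

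With baseline CMS in the model, this contrast still addresses the difference in 12-month improvement. Use the same model, through its group-by-visit terms, in place of the exploratory mixed ANOVA. A sensitivity analysis for data not missing at random is optional.

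Cost: analysis wording and syntax only. Sample size, visits and data collection stay as they are. When the article was submitted, 118 participants had been enrolled and the study was to be finalised in 2023, so the change could be fixed before the analysis. The downsides are small: the model is slightly more complex, it adds little or nothing for patients lost before the 8-week visit, and its protection relies on dropout being explained by the observed scores.

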### Sample size calculation

For the sample size calculation, we used the minimal clinically important difference (MCID) for the Constant Murley Score as determined by the study of Kukkonen et al [24].

The reported MCID over a period of 12 months was 10.4 points, with a mean Constant Murray Score of 53.1 (standard deviation of 17.2) at baseline [24].

We aim to find a superiority of one of the two treatment options to treat patients with calcifying tendinitis of the shoulder. Our hypothesis is that superiority of NACD or ESWT above the other treatment in functional recovery over a period of 12 months will be found. Superiority will be expressed by an additional effect size of minimally 0.5. Using a standard deviation of 17.2 of the CMS, we aim to detect a minimally difference of 8.6 points between both groups. Using a power of 80% and an alpha of 0.05 the required sample size is 63 patients per group, resulting in a total of 126 patients. With this number of patients, we will also able to detect a MCID between both groups of 10.4 points (required number of patients is 43 per group). The final sample size required is 140 patients, to accommodate 10% potential dropout rate over 1 year.

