**Methods:**

Following a power calculation using the minimal clinical important difference of our primary outcome (Constant-Murley score, CMS) 140 patients will be included in the study. Enrolment is based upon strict inclusion/ exclusion criteria outlined in the Methods section. Participants will be randomized by computer in two groups (e.g. 70 patients will receive NACD and 70 patients will receive ESWT). The NACD treatment will consist of a sonographically guided removal of the calcific deposits and the ESWT treatment will be a focused ESWT. Both treatments will be conducted according to a standardized protocol, as part of care as usual in our hospital. The primary outcome will be the between group differences in functional outcome (measured with the CMS) between baseline and after 12 months follow-up. Secondary outcomes will be questionnaires regarding the clinical outcome (SST) and quality of life (EQ-5D-5L). Furthermore, NRS pain and cost related questionnaires (iPCQ and ProDisQ) will be collected during follow-up after two months, six months and at final follow-up after 12 months.

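### The 80% power for 8.6 points uses a baseline SD of the CMS, but the primary analysis is of change and no SD of change or correlation is given

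*Protocol article*

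**What the plan says.** The section Sample size calculation takes its SD from the study that supplied the MCID, "with a mean Constant Murray Score of 53.1 (standard deviation of 17.2) at baseline". The target is set first as a standardised effect: "Superiority will be expressed by an additional effect size of minimally 0.5". It is then turned into points: "Using a standard deviation of 17.2 of the CMS, we aim to detect a minimally difference of 8.6 points between both groups". The result follows: "Using a power of 80% and an alpha of 0.05 the required sample size is 63 patients per group". The same section adds that this number also covers the "MCID between both groups of 10.4 points (required number of patients is 43 per group", and it ends: "The final sample size required is 140 patients, to accommodate 10% potential dropout rate over 1 year".

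The section Statistical analyses specifies for the primary outcome "linear regression analyses with change in CMS between baseline and 12 month follow up as dependent variable". The section Outcome measures likewise defines the primary outcome between baseline and 12 months. Baseline CMS is not named as a covariate. Baseline variables enter the model if they move the treatment estimate by more than 10%.

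**The concern.** The SD in the calculation and the variable in the analysis do not match. An SD at one visit describes how patients differ from each other at that visit. The SD of change also depends on the SD at 12 months and on how strongly the two visits correlate. The article states neither of these, nor the SD of change itself, so a reader cannot tell whether 17.2 is too large, too small or about right for the planned analysis.

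The interpretation of a null result is at stake. The trial seeks to name a preferable treatment and to inform shared decisions. If no difference is found, the result will be read against a stated 80% chance of detecting 8.6 points, and for an unadjusted change score that chance could be materially lower. This is not detail that an article normally leaves to an analysis plan: the article itself states the SD, its source, the target, the power and the model.

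**Working it through.** **Inputs.** SD 17.2 (baseline, cited study), target differences 8.6 and 10.4 points, alpha 0.05 (two-sided, which reproduces the plan's figure), power 80%, 63 per group, 10% dropout: all from Sample size calculation. Equal allocation is from the abstract: "70 patients will receive NACD and 70 patients will receive ESWT". The correlation rho between baseline and 12-month CMS and the 12-month SD (SD12) are not in the document. They are assumptions here and are shown as ranges.

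**1. The plan's own figures.**
- n per group = 2(1.96 + 0.8416)² × (SD/difference)².
- For 8.6 points: 2 × 7.849 × (17.2/8.6)² = 62.8, so 63 per group and 126 in total.
- For 10.4 points: 2 × 7.849 × (17.2/10.4)² = 42.9, so 43 per group.
- Dropout: 126/0.9 = 140.

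All four stated figures reproduce.

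**2. SD of the analysed variable.**
- Change score, no baseline covariate: SD = √(17.2² + SD12² − 2·rho·17.2·SD12). With SD12 = 17.2 this is 17.2·√(2(1 − rho)).
- With baseline CMS as covariate: SD = SD12·√(1 − rho²). The treatment estimate is then the same whether change or the 12-month score is the dependent variable.

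**3. Power with 63 per group and SD12 = 17.2.** Noncentral t with noncentrality difference/(SD·√(2/63)). The normal approximation gives values up to about one percentage point higher.

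| rho | SD of change | 8.6 points, unadjusted | 10.4 points, unadjusted | SD given baseline | 8.6 points, baseline CMS as covariate |
|---|---|---|---|---|---|
| 0 | 24.3 | 50% | 66% | 17.2 | about 80% |
| 0.2 | 21.8 | about 60% | 76% | 16.9 | 81% |
| 0.3 | 20.4 | 65% | 81% | 16.4 | 83% |
| 0.4 | 18.8 | 72% | 87% | 15.8 | 86% |
| 0.5 | 17.2 | about 80% | 92% | 14.9 | about 90% |
| 0.6 | 15.4 | 88% | 96% | 13.8 | 94% |

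**4. The threshold.** The SD of change equals 17.2 when SD12² = 2·rho·17.2·SD12, that is, when rho = SD12/(2 × 17.2). This is 0.35 for SD12 = 12, 0.41 for 14, 0.50 for 17.2, 0.58 for 20 and 0.64 for 22. For 10.4 points with equal SDs, 80% power holds down to rho of about 0.27 (normal approximation).

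**5. The 10% rule.** This was simulated with 63 per group, a true difference of 8.6, equal SDs, normal scores, baseline CMS as the only candidate covariate, and 10,000 trials per value of rho. Baseline CMS entered in 78% of trials at rho 0, 73% at 0.2, 69% at 0.3 and 64% at 0.4. Power was 74%, 77%, 80% and 83%. The tests took no account of the selection step.

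**6. Limit of the covariate remedy.** With SD12 = 20, the adjusted SD is 20 at rho 0 and 20·√(1 − 0.09) = 19.1 at rho 0.3. Power for 8.6 points is then about 67% and 71%.

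**7. Adjusted against unadjusted.** The variance of change minus the adjusted variance is (17.2 − rho·SD12)², which is never negative. Apart from one degree of freedom, adjustment for baseline CMS cannot cost precision.

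**The case against.** Four points can be made for the plan.

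- **The target is a standardised effect of 0.5, for which 63 per group is right whatever the SD.** True, but the plan also states the target in points, and that translation depends on the SD. If 0.5 is meant in units of the SD of change, then with equal SDs and rho 0.2 it corresponds to 0.5 × 21.8 = 10.9 points, not 8.6.
- **The 10% rule may bring baseline CMS into the model.** This stands in part. Under the rule, simulated power is well above the unadjusted figures and reaches about 80% at rho 0.3. But the data decide whether the covariate enters, and at rho 0 to 0.2 simulated power stays below 80%. The rule does not secure the stated power.
- **The protocol's clinical benchmark is 10.4 points, and for that the trial is better protected.** This stands. The exposure is mainly to differences below the MCID.
- **The 12-month SD may be smaller than 17.2.** It may, and the threshold then falls below 0.5. It may also be larger. The document does not say.

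A reader might go further and infer that the trial is underpowered, that more patients are needed, or that the stated power fails outright below a correlation of 0.5. The document supports none of these. The correlation and the 12-month SD are unknown, power exceeds 80% over part of the plausible range, and the 0.5 threshold applies only with equal SDs and no baseline covariate.

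**Conclusion.** The point holds in conditional form. The sample size uses a cross-sectional baseline SD for an analysis of change, and nothing in the article links the two. With a 12-month SD of 17.2 and no baseline covariate, power for 8.6 points with 63 per group runs from about 60% at rho 0.2 to 88% at rho 0.6, and reaches about 80% only at rho of about 0.5 or more. With another 12-month SD, the threshold is SD12/(2 × 17.2). The fault is an unsupported input, not a miscalculation, and it concerns the 8.6-point claim far more than the 10.4-point one. What can be said is that the 80% for 8.6 points is unsupported as written. The point is worth correcting because the remedy is cheap and the figure will frame a null result.

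**What to change.** Name baseline CMS as a fixed covariate in the primary regression, whatever the 10% rule gives, and say in the sample size paragraph that 17.2 is the SD of the score at one visit. With that covariate, 63 per group give about 80% power or more for 8.6 points at any correlation, provided the 12-month SD is no more than about 17.2. State that condition beside the figure.

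If the unadjusted change score is kept, restate the power for 8.6 points as a range over the correlation and the 12-month SD, or give a sourced SD of change.

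Keep the total at 140. The cost is a rewording of two paragraphs and one degree of freedom. Baseline CMS is already collected under the data collection schedule, and no extra patients or visits are needed. The article reports 118 participants at submission, so the covariate should be fixed in a dated amendment or in the analysis plan before the outcome data are analysed.

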## Discussion

This RCT study is the first to compare NACD and a single session of focused ESWT as treatment for conservative therapy resistant calcific tendinitis of the shoulder. The results of this study will aid the physician as it provides valuable information for a shared decision strategy in which treating physician and patient determine the most appropriate treatment. Furthermore, the cost-effectiveness analysis can assist the physician and health care institution to decide whether to provide a certain treatment for conservative therapy resistant calcific tendinitis of the shoulder.

The inclusion period was initially supposed to be approximately two years. In 2015 and 2016 a total of 140 patients with conservative therapy resistant calcific tendinitis of the shoulder were treated with either NACD or ESWT in the Máxima Medical Centre. It was the expected that almost all of these patients would have been eligible candidates for the current study. Although it was expected that 10% of these patients would not be willing to be randomized or comply to the study protocol. Therefore, an inclusion period of two years seemed feasible. However, in the first year the recruitment was slower than expected because more patients than anticipated did not fulfill the in- and exclusion criteria. Therefore, an amendment to the original protocol was made to extend the inclusion period. As a result of the global COVID-19 pandemic, the Orthopaedic outpatient clinic was temporarily closed and the inclusion ceased for a short period. Several attempts were made to speed up the inclusion rate. The first was to include another hospital as participating center for the study. However, this turned out not to be possible because other surrounding hospitals did not offer focused ESWT treatment. The second was to request the department of Rheumatology at the Máxima MC as well as all physical therapists in the region to refer their patients with calcifying tendinitis to the Orthopaedic outpatient clinic for possible inclusion. Inclusion rate are now according to the adjusted feasibility rate. Besides slowing down recruitment, COVID-19 also influenced the follow-up. Patients were not allowed to visit the Orthopaedic outpatient department. As a result, the follow-up of a small number of patients (*n* = 12) was administrated by phone call or video call. This was especially challenging when determining the items abduction, anteflexion and force of the CMS, which requires specific physical examination and testing. In order to obtain the necessary information as reliable as possible one single outcome assessor gave specific instructions to the patient, mainly by explaining the patient how range of motion is determined. Although, the contribution of these items to the total score of the CMS (45 out of 100 points) is considerable in one patient. One should take into consideration that only a small amount of the measurements was done in this manner and they were equally divided between the two groups (seven in NACD group and five in ESWT group). Therefore, the research team expects that potential bias due to this digital compared to in person assessment of the CMS was negligible. Furthermore, the number of patients in which digital assessment was performed was equally distributed between both groups.

Considering the extended inclusion period, additional outcome assessors joined the research team during the execution of the study. The primary investigator trained these assessors to make sure that all measurements were done according to the protocol. In addition, the principal investigator observed the execution of several measurements and give feedback in order to minimize variability in the assessment of the CMS, a measurement which showed good inter-observer reliability in the past [19]. Radiologically assessment will be performed by the principle investigator. In addition, all sessions of focused ESWT treatment will be performed by the same experienced health care professional. Multiple radiologists will perform the NACD treatment, all having a comparable and extensive experience in sonographically guided interventions. Health care professionals performing the ESWT or NACD treatment will not explicitly be informed that the patient is participating in the current study. As a result, it is expected that all performed treatments will be of a comparable high standard.

Despite these precautions, a potential source of bias in the current study might be information bias. Considering the content and logistics of the treatments under investigation, patients and outcome assessors cannot be blinded for treatment allocation. However, since patients at the start of the study are informed that it is not yet known which treatment will lead to the best results and most likely only patients without a pre-existing treatment preference will participate in a RCT, this potential source of bias seems to be small. In addition, outcome assessors will not be the referring shoulder surgeon of the participating patients.

Overall this study will provide more insight regarding treatment for conservative therapy resistant calcific tendinitis of the shoulder by comparing NACD directly to focused ESWT, which will aid the physician and patient in determining the appropriate treatment plan. At time of manuscript submission 118 participants had joined the trial. Current protocol version is 6. The first patient was included in May 2018; the aim is to fulfill the inclusion in 2022 after which the study will be finalized in 2023.

